#### Statistical analysis

Random allocation should help us control for possible extraneous variations. However, we are also measuring and controlling for known extraneous variables (if needed) that could influence our primary outcome. Age, education, income, and cancer stage have been identified as possible predictors of FCR [3, 10]. These are being considered as potential covariates and are measured at baseline (T1).

Descriptive statistics are being used to present the study participants’ characteristics. To determine the effectiveness of our intervention, we are using advanced regression analysis. Kaplan-Meier curves, period prevalence, and cumulative risk models may be used to explain the time-event analysis. To analyse data from across the four-time points (T1-T4), we are using Generalized Estimating Equations (GEE) models, with factor-specific events for each of the outcome variables. Similar sensitivity analyses are to be used to assess the effect of the FORT intervention on the secondary outcomes. All models will be adjusted for adverse events and other potential confounders. We will also assess treatment benefits for subgroups of participants by analyzing their sociodemographic, clinical, and psychological characteristics [79]. To identify key variables that lead to changes in our outcome variables, we are taking two approaches to selecting the variables for our regression analyses, including intermediate variables. In the first approach, variables will be selected based on background knowledge and the relationship of the variable to intervention and outcomes. Our second approach relies primarily on high-dimensional, automatic variable selection techniques, such as forward and backward selection, and automatic high-dimensional ‘Proxy’ adjustment [80]. In our opinion, combining these two approaches yields more unbiased estimates. For the above analyses, we will use the statistical software packages IBM SPSS Statistics 22.0 and STATA 14.

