**Methods:**

Sixteen groups of seven to nine women are being allocated to the intervention or the control group. The control group receives a 6-week, 2 h, structurally equivalent support group. We are recruiting 144 cancer survivors from four hospital sites in three Canadian cities. The sample size was based on the moderate pre/post-test changes found in our pilot study and adjusted to the drop-out rates. *Measurements*: The primary outcome, FCR, is measured by the Fear of Cancer Recurrence Inventory. Secondary outcomes measured include cancer-specific distress, perceived risk of cancer recurrence, illness uncertainty, intolerance of uncertainty, coping, and quality of life. We use reliable and recognized valid scales. Participants are to complete the questionnaire package at four times: before the first group session (baseline), immediately after the sixth session, and 3 and 6 months post-intervention. *Analysis*: In the descriptive analysis, comparison of group equivalent baseline variables, identification of confounding/intermediate variables and univariate analysis are planned. Each participant’s trajectory is calculated using Generalized Estimating Equation models to determine the time and group effects, after considering the correlation structures of the groups. An intent-to-treat analysis approach may be adopted.

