### Randomization of participants

Before randomization, all of the following forms are completed by all eligible and consenting participants: (a) eligibility form, (b) consent form, (c) baseline measures, and (d) baseline interview form. Randomization of all recruiting sites is centralized at one recruiting site and is performed by a biostatistician working at arm’s length from the study. The biostatistician does not know the identity of the therapists and gives the group allocations to the study’s RA. The group allocation is concealed to the participants. The participants do not know which groups comprise the FORT intervention or the structurally equivalent control group. Randomization occurs each time 18 BC survivors or 18 GC survivors are deemed eligible at one of the four sites. This ratio of 18 ensures nine women in each group, with a buffer of at least two probable dropouts per group. We achieved this target in our pilot study. Each group is planned to start within 2 weeks of the initial randomization of women to each study arm.

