#### Sample size

The primary study outcome is FCR, as measured by the FCRI [9]. The sample size was calculated based on the moderate changes in FCR we observed in the pilot study from baseline (T1) to 3 months post intervention [27] and in the only published RCT intervention study that addresses the fear of disease progression [78]. A sample size of at least 112 participants ensures our ability to detect an effect size of 0.40, with a power of 0.95 and an alpha level of .05 between pre- and post-intervention FCR measures. Therefore, we plan to recruit eight groups of seven participants, for a total of 56 participants per arm. We are also enrolling an additional two participants per group per arm, to account for possible dropouts (72 per arm). This strategy will yield 144 participants in total.

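### The GEE takes T1 to T4 as outcomes without naming the tested contrast or how baseline is used, and does not name site or cancer type as covariates; fixing these terms gains precision at almost no cost

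*Protocol article*

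**What the plan says.** - **Analysed visits.** Protocol article, Statistical analysis: "To analyse data from across the four-time points (T1-T4), we are using Generalized Estimating Equations (GEE) models". T1 is therefore one of the modelled time points. The outcomes section places it two weeks before the intervention, and the randomisation section requires baseline measures before allocation.
- **Terms named.** Abstract, Methods: "Generalized Estimating Equation models to determine the time and group effects". No interaction, baseline covariate or equal-baseline constraint is mentioned there or in the Statistical analysis section.
- **Covariates named.** Statistical analysis: "Age, education, income, and cancer stage have been identified as possible predictors of FCR". They are candidates, used only if needed. The section also leaves room for other confounders and for two routes of variable selection, one of them automated.
- **Structure of randomisation.** Randomization of participants: "Randomization occurs each time 18 BC survivors or 18 GC survivors are deemed eligible at one of the four sites". Allocation is thus balanced within sets defined by site and cancer type.
- **Hypotheses.** Research question and hypotheses: differences between arms just after the intervention (T2) and at three and six months (T3, T4).
- **Size.** Sample size: "A sample size of at least 112 participants ensures our ability to detect an effect size of 0.40". The target behind that number is 95 % power at the 5 % level, and it comes to 56 women in each arm, in eight groups of seven.

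**The concern.** Because T1 is measured before allocation, the arms have the same expected score there. The T1 score can serve in three ways, and they are not equally good. As one more outcome under a group main effect, it averages a known zero into the treatment effect. As the reference visit of an unconstrained group-by-time contrast, it gives a change-score comparison, which is unbiased but carries the full noise of the baseline. As a covariate, or as an outcome with the arms held equal at T1, it removes variance at no cost in bias. The article commits to T1 to T4 in the model but does not say which of these applies, and neither of the first two is the best use of data already collected.

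Site and cancer type define the sets within which women are allocated. If they are left out, or a stepwise routine drops them, any outcome difference between sites or cancer types stays in the residual variance, although the design has already removed it from the true error of the comparison.

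**Working it through.** **The plan's own figure.** The inputs are a difference of 0.40, alpha 0.05 and power 0.95. The metric and sidedness are not stated; I take SD units and two-sided. A plain two-arm comparison needs n = 2(1.960 + 1.645)²/0.40² = 162.4, so 163 per arm. With 56 per arm its power is about 0.56. The stated 112 does not follow from that reading. This is a separate matter; it matters here only because there is little precision to spare.

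**Assumptions.** 56 per arm, a true difference of 0.40 SD that is constant over T2 to T4, equal variances, one common correlation r between visits, no clustering, two-sided t test. The document gives no r; I use 0.5, 0.6 and 0.7.

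**Effect and variance per woman (in SD²) for three analyses:**

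1. Group main effect over T1 to T4: effect (0 + 3 × 0.40)/4 = 0.30; variance (1 + 3r)/4.
2. Unconstrained group-by-time, mean of T2 to T4 minus T1: effect 0.40; variance (1 + 2r)/3 + 1 − 2r.
3. Mean of T2 to T4 adjusted for T1: effect 0.40; variance (1 + 2r)/3 − r².

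| r | Var 1 | Var 2 | Var 3 | Power 1 | Power 2 | Power 3 |
|---|---|---|---|---|---|---|
| 0.5 | 0.625 | 0.667 | 0.417 | 0.512 | 0.729 | 0.902 |
| 0.6 | 0.700 | 0.533 | 0.373 | 0.469 | 0.819 | 0.930 |
| 0.7 | 0.775 | 0.400 | 0.310 | 0.432 | 0.913 | 0.965 |

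Analysis 2 has 1.60, 1.43 and 1.29 times the variance of analysis 3. For analysis 1, variance divided by squared effect is 2.67, 3.33 and 4.44 times that of analysis 3 (for example 0.625/0.75²/0.417 = 2.67).

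**One follow-up visit alone.** The change score has variance 2(1 − r) and the baseline-adjusted score 1 − r², so the adjusted variance is (1 + r)/2 of the other: 0.75, 0.80, 0.85. Power is 0.555, 0.650 and 0.773 for change, against 0.678, 0.746 and 0.836 adjusted.

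**With clustering.** An intraclass correlation of 0.05 (assumed), groups of seven and a normal approximation lower every figure but keep the order: analysis 2 gives 0.62, 0.72 and 0.84; analysis 3 gives 0.82, 0.86 and 0.92.

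**Site and cancer type.** Suppose they explain 2 to 10 % of residual variance (assumed).

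- With individual-level standard errors, a single visit and r = 0.6, omitting them gives power 0.756 to 0.765 and including them 0.762 to 0.796, a gain of about 1 to 3 points. The test without them is conservative: its true size is 0.048 to 0.039 instead of 0.05.
- With standard errors built on the 16 therapy groups (mean of T2 to T4, r from 0.5 to 0.7, intraclass correlation 0 to 0.05), the gain runs from about 1 to about 15 points.
- In neither case is the estimate biased, because the arms are balanced within each set of 18.

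**The case against.** **Dilution.** A reader might infer from the abstract's wording that the plan dilutes the treatment effect. The document does not support that as a fact. No passage fixes the tested term as a group main effect over all four visits. The hypotheses are about T2, T3 and T4, the abstract speaks of each participant's trajectory, and the sample size is framed as a comparison "with a power of 0.95 and an alpha level of .05 between pre- and post-intervention FCR measures". All of these fit a group-by-time or change contrast better. The objection stands: the 0.30 SD figure is conditional.

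**T1 as an outcome.** A reader might also take the presence of T1 in the outcome vector for an error. It is not one. With the arms constrained equal at T1 the model is as efficient as one with T1 as a covariate, and even the unconstrained contrast is unbiased. What remains is that no such constraint is stated.

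**Site and cancer type.** They are not excluded. The covariate list is open, and the rationale for enrolling two cancer types acknowledges added confounding factors to control. The same part of the article reports few differences in fear of recurrence by cancer type, so the gain from that factor may be small. Still, factors that define the randomisation should not depend on an if-needed clause or on stepwise selection.

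**Level of detail.** A condensed article may leave model terms to an analysis plan. That answers silence, but this article does state the visits, the effects and the candidate covariates, and what it states does not match its own time-specific hypotheses.

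**Conclusion.** The concern holds as a matter of precision and of an unnamed contrast, not of bias. On the more likely group-by-time reading, power for the mean of T2 to T4 is about 0.73 to 0.91, where baseline adjustment would give 0.90 to 0.965. On the less likely main-effect reading, the effect falls from 0.40 to 0.30 SD and power to 0.51 to 0.43. Baseline handling is the main part; site and cancer type are secondary, and their value depends on how far outcomes differ by them and on the level at which standard errors are built.

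The correlations, the constant effect, the SD metric for 0.40 and the absence of clustering are my assumptions. Enrolling only women above a severity cut-off may lower the correlation between baseline and follow-up, and with it the gain over an unadjusted follow-up comparison. The advantage over the change score does not vanish for that reason: it is larger at lower correlations.

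**What to change.** State in the Statistical analysis section, or confirm in the analysis plan, that:

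1. The treatment effect on FCRI is the group contrast at the named follow-ups T2, T3 and T4, from a model with group, time and group-by-time.
2. T1 FCRI enters as a covariate with T2 to T4 as outcomes. Equivalently, T1 stays an outcome with the arms constrained equal there. In a GEE this second form needs a working correlation other than independence; otherwise T1 adds no information on the follow-up contrasts.
3. Site and cancer type are fixed terms in every model and are exempt from variable selection.
4. Each secondary outcome is handled in the same way with its own baseline.

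This needs no new data and no further participants. Four sites and two cancer types take at most 3 + 1 = 4 degrees of freedom. If inference is based on the 16 therapy groups, these come out of about 16 − 2 = 14.

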#### Potential covariates

As group cohesion may influence the intervention’s impact, we measure group cohesion at the end of each 6-week FORT-intervention group and each 6-week control group intervention. Cohesion is measured using the *Group Cohesion Scale − Revised* [74], a 25-item scale measuring interaction and communication among group members. For example, one item is “Group members usually feel free to share information.” The Cronbach’s alpha internal consistency of this scale ranged from .77 to .90 during post-test assessment [74].

Group alliance within therapy groups can be therapeutic in and of itself and can enhance intervention efficacy [75]. That is, patients who perceive improvements during their therapy are more likely to have positive feelings towards the therapist, be more committed to treatment, and work more collaboratively. We measure group alliance using the *California Psychotherapy Alliance Scale* [76], a 24-item scale with four theoretically derived dimensions: (a) the therapeutic alliance, (b) the working alliance, (c) the therapist’s contribution to the alliance, and (d) the agreement on goals and tasks of therapy. We measure therapeutic-working-group alliance immediately following the last sessions of both the intervention and the control groups.

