Treatment credibility and participants’ expectancy for improvement are two additional variables that may contribute to alternative explanations of differences found between two compared conditions [77]. To assess credibility and expectancy to ensure initial equivalency between the FORT intervention and the structurally equivalent control group, we are using the *Credibility/Expectancy Questionnaire* (CEQ) [77]. The CEQ has 6 items; three items relate to the credibility factor (“think” questions), and three items relate to the expectancy factor (“feel” questions). Each factor demonstrates high internal consistency (α = 0.81 for expectancy and α = 0.86 for credibility) and a good Cronbach’s alpha for the whole scale (α = 0.85) [77]. Test-retest reliability over a 1-week period scored at 0.82 for expectancy and 0.75 for credibility [77]. The CEQ has two ratings; one is from 1 (not at all) to 9 (very much), and the other from 0 % (not at all) to 100 % (very much). Scoring involves transforming the percentage to a number between 1 and 9, giving both scales a range from 3 to 27. The CEQ is given to participants immediately after the end of Session 1, in which the study intervention is explained. Both the FORT intervention and the control group members complete this scale.

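### All models are to be adjusted for adverse events, and intermediate variables are among those selected for the regressions; both arise after randomisation, and adjusting for them can bias the estimated FORT effect

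*Protocol article*

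**What the plan says.** The Statistical analysis section of the protocol article assigns the question of effectiveness to regression, with GEE models over T1 to T4. It then sets a rule without exception: "All models will be adjusted for adverse events and other potential confounders".

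On choosing variables it says: "we are taking two approaches to selecting the variables for our regression analyses, including intermediate variables". Under the first approach, "variables will be selected based on background knowledge and the relationship of the variable to intervention and outcomes". For the second: "Our second approach relies primarily on high-dimensional, automatic variable selection techniques, such as forward and backward selection", together with automatic proxy adjustment. The reason given is: "In our opinion, combining these two approaches yields more unbiased estimates". The Abstract also plans to identify confounding and intermediate variables.

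The same section names age, education, income and cancer stage as possible covariates. They are measured at T1 and are to be controlled for only if needed. No sentence sets apart a primary model restricted to such baseline variables.

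**The concern.** Randomisation already balances confounders in expectation. A variable that arises after allocation cannot be a common cause of allocation and outcome, but allocation can change it. Conditioning on such a variable has two possible consequences. If part of the FORT effect on FCR passes through it, the treatment coefficient loses that part. If it shares an unmeasured cause with FCR, conditioning on it can create an arm difference where none exists.

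This matters for FORT because the article's account of the intervention says that it works by changing perceived risk, coping, uncertainty and intolerance of uncertainty. Variables chosen for their relation to both intervention and outcome could well be these mechanisms. The reported coefficient might then not be the effect of assignment to FORT, which is what the main hypothesis concerns. It could also depend on which variables an algorithm kept.

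**Working it through.** The article gives no figure on this point to reproduce. The check therefore sets out the timing of each variable and then illustrates size under stated assumptions.

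**1. Timing and stated role**

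| Variable | When it arises | Role the article gives it |
|---|---|---|
| Age, education, income, stage | T1, before randomisation | Possible covariates, if needed |
| Adverse events | After randomisation | Adjusted for in all models |
| Intermediate variables (not named) | After randomisation, by definition | Among the variables selected for the regressions |
| Group cohesion, alliance | "we measure group cohesion at the end of each 6-week FORT-intervention group and each 6-week control group intervention"; alliance follows the last session | Listed under Potential covariates; no sentence enters them in a model |
| Credibility/expectancy (CEQ) | "The CEQ is given to participants immediately after the end of Session 1" | Check on initial equivalence of the arms |

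Only the first row is safe by design as an adjustment set for the treatment effect. The second and third rows are the ones the text puts into models.

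**2. Adjusting for an intermediate**

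The Sample size section supplies the scale: effect 0.40, 56 women per arm. Assumptions: unit variances, mediated share *s*, mediator-outcome slope *b*.

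- Mediator: M = aT + error, with a = 0.40·s/b.
- Outcome: Y = (1 − s)·0.40·T + bM + error.
- Total effect: (1 − s)·0.40 + ab = 0.40.
- Coefficient of T once M is in the model: (1 − s)·0.40.

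Simulation with b = 0.4 and 4,000 runs per row:

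| Share mediated (assumed) | Formula | Simulated coefficient | Power with M | Power without M |
|---|---|---|---|---|
| 0% | 0.40 | 0.40 | 0.63 | 0.56 |
| 25% | 0.30 | 0.29 | 0.38 | 0.55 |
| 50% | 0.20 | 0.20 | 0.20 | 0.55 |
| 100% | 0.00 | 0.00 | 0.05 | 0.56 |

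The power column depends on *b*, because the mediator also absorbs residual variance. Over b = 0.2 to 0.6, power is 0.30–0.45 at a 30% share and 0.16–0.25 at 50%. These figures also ignore repeated measures, baseline adjustment and clustering, so they show direction and are not forecasts. Whether 56 per arm supports the planned power is a separate question, and nothing here depends on it.

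**3. Adjusting for a variable that shares a cause with the outcome**

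Suppose there is no treatment effect. Let allocation shift the variable by *a* SD, and let an unmeasured cause load *U* on both it and FCR. With unit variances the adjusted coefficient is −aU².

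- a = 0.3, U = 0.5: −0.3 × 0.25 = −0.075 (simulated −0.074); type I error 0.07.
- a = 0.8, U = 0.7: −0.8 × 0.49 = −0.392 (simulated −0.393); type I error 0.60.

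The nominal level is 0.05. The path strengths are assumed, and the sign of the bias depends on the signs of the paths.

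**4. Forward selection alone**

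Treatment forced in, baseline candidates, entry at p < 0.05, no treatment effect, 112 women:

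| Candidates (assumed) | Runs | Type I error |
|---|---|---|
| 10 | 1,500 | 0.059 |
| 20 | 1,000 | 0.060 |
| 50 | 300 | 0.113 |

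The simulation standard error at a true 0.05 is √(0.05 × 0.95 / runs): 0.006, 0.007 and 0.013. The first two results lie within two standard errors of 0.05; the third clearly does not.

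**The case against.** The strongest reply is that most of this describes exploratory work. The sentence on selection opens with the aim of finding key variables behind changes in outcomes and follows directly on subgroup analysis. The Discussion names understanding of FCR predictors as a contribution in its own right. The sentences on effectiveness and GEE come earlier and do not mention selection. That reading is possible, so the text does not establish that automatic selection or intermediates belong to the primary model. It does not settle the matter either: the stated reason is less biased estimates, which is an argument about effect estimation. Nor does it touch the adverse-event sentence, which covers all models.

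Three stronger readings are tempting and are not supported.

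- A reader might infer that cohesion, alliance and CEQ enter the effect model, since all three sit under Potential covariates. No sentence says so, and CEQ is described as an equivalence check.
- A reader might infer that stepwise selection makes the p-values worthless. With 10–20 candidates the inflation is small, and the article gives no candidate count.
- A reader might take the shrinkage or power figures as the expected loss. The mediated shares are assumed and concern intermediates. The article gives no rate or definition of adverse events, so the effect of adjusting for them cannot be sized.

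It is also fair to say that a condensed article may leave the exact covariate list to the analysis plan. The point here is a rule that the article does state.

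**Conclusion.** The concern holds in this limited form. The article prescribes adjustment of every model, the effectiveness GEE included, for a post-randomisation variable. It admits intermediates and automatically selected variables to its regressions without confining them to exploratory use, and it defends this by a bias argument that does not apply to a randomised comparison.

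Such adjustment can bias the treatment effect; the documents do not show that it will, or by how much. If 25–50% of a true 0.40 SD effect ran through an adjusted intermediate, the estimate would be about 0.29–0.20 SD. If no effect ran through it and there were no shared cause, the estimate would stay at 0.40. P-values after automatic selection may depart from the nominal level, little with a short candidate list and more with a long one. The wording should be corrected before analysis because it bears on the primary result.

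**What to change.** - Delete adjustment for adverse events, and tabulate them by arm.
- State that the primary treatment-effect GEE uses only prespecified baseline covariates, for example the T1 value of the outcome and whichever of age, education, income and stage are chosen in advance. The final list can stand in the analysis plan.
- State that intermediates, any automatic selection or proxy adjustment, and cohesion, alliance and CEQ if modelled at all, are confined to labelled exploratory mediation or predictor analyses.
- Remove the claim of less biased estimates as far as it concerns the treatment effect.

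The cost is wording only. Recruitment, measurement and sample size stay as they are, and every variable collected keeps a use.
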